### Randomization

Upon study enrollment, the participants with multimorbidity at each site will be randomly assigned to 1 of 3 equal-sized trial arms (ie, 80-100 participants with multimorbidity will be assigned to each arm). Block randomization will be implemented to ensure balance in the sample size across groups; given that there are 3 arms, a block size of 9 will be implemented (ie, participants will be block randomized per every 9 individuals). The block randomization will be set up in REDCap [49,50].

Following CONSORT (Consolidated Standards of Reporting Trials) guidelines for p-RCTs [52], this trial will be unblinded. Blinding the researchers to participants’ trial arms will not be possible due to the clear differences in the technology components across groups (eg, no component will be assigned to participants in trial arm 3). Additionally, it will not be possible to blind participants to the allocation of study or technology components.

### Data Analysis Plan

For the p-RCT primary outcomes, three types of analysis will be conducted: (1) What is the influence of ProACT on perceived QoL? (2) What is the influence of ProACT on HCU? (3) What trial arm is the most cost-effective?

To determine if significant differences exist in (1) perceived QoL between the arms and (2) HCU between the arms, a linear mixed model will be used. In this model, a 2-level structure will be applied; repeated measures of QoL or HCU will comprise the first level, and participants will comprise the second level in the hierarchy. The outcomes will be assessed longitudinally using fixed effects of time, treatment arm and time interaction, and other baseline covariates such as age and gender.

ProACT’s cost-effectiveness will be determined with the use of 2 economic evaluation techniques, cost-effectiveness standard and cost-utility analysis, applying the societal perspective. Societal perspective means, in general terms, the effectiveness evaluation will consider all the relevant contributors related to the participant. The 2 methods will allow the determination of the monetary value and the benefits of the intervention in health terms. For the monetary value, the HCU data will form the basis of the analysis.

Due to the questionnaire construction variation (countable and binary questions) and the time points of data collection during the trial, the analysis will make use of 3 statistical models: Poisson (countable data), logistic (binary response data), and linear regression (continuous data). The analysis will allow the observation of how ProACT affects the HCU, per arm at each trial site, and what the costs involved in this effect are for the monetary value definition. To define a 95% CI for this cost-effectiveness estimate per arm and per trial site, a sensitivity analysis will be performed, for instance, using a bootstrapping methodology.

Indirect costs of the care network (informal care) will be calculated using data collected from the participants with multimorbidity and their informal caregivers. First, participants with multimorbidity will provide data on time spent on care by their informal caregivers. With the use of the opportunity costs method, this time will be converted into monetary value. Next, data collected from the informal caregivers, via the Zarit Burden Interview, will facilitate an assessment of the health gains of the time spent in care, considering the ProACT intervention. Indirect costs will be considered as an aggregated cost in this study.

The cost-utility analysis technique will underpin the quality-adjusted life years calculation. The quality-adjusted life years is a general measure used in economic evaluation that permits the valuation and comparison of the health gains of an intervention. For this calculation, the health-related QoL measurement instrument (EQ-E5-5L) will capture the self-perceived health status of the participant in a 5-digit code. Next, the code will be converted into a utility value (or utility weight), based on the country-specific value set. The result consists of the multiplication of the utility value with the period lived with the self-perceived condition.

For the secondary outcomes, such as the impact of ProACT on self-management, we may use structural equation modeling to determine the relevance and importance of different variables measured during the trial. Hitherto, there is no consensus on how to measure improved self-management. For this study, we may consider the concept of self-management as a composite measurement of different variables proven to be associated with the ability to self-manage chronic illnesses. Variables that are associated with improved self-management include, for instance, self-efficacy, health literacy, and disease knowledge, and therefore may be treated as latent variables. Using a structural equation model, such as confirmatory factor analysis, we will be able to identify the existence of a relationship between these variables and an overarching concept of self-management.

Outcomes from this exploratory analysis will help to determine whether features in ProACT could be tested in future clinical trials. Outcomes from the process evaluation and their inclusion, where possible, in the aforementioned exploratory analysis may also help to determine the relationship between implementation and effectiveness, and for whom, in what circumstances, and how ProACT influences the primary and secondary p-RCT outcomes. Descriptive summary statistics will be collated on the primary and secondary outcome measures, as well as on the variables included in the exploratory analysis.

The process evaluation will draw upon a range of quantitative and qualitative data to explore the implementation of ProACT and the factors that impact upon it. Descriptive summary statistics will be collated and examined where applicable (eg, demographic and system use data for participants with multimorbidity and care network participants, partner organizations’ administrative and ProTransfer data, and participant recruitment and withdrawal data).

Interview and focus group data will also be attained to explore implementation and factors associated with it, including, for example, the perceived usability, accessibility, and acceptability of, and engagement, satisfaction, and overall experiences with, ProACT. The interviews and focus groups will be audio recorded, transcribed, and imported into NVivo (QSR International; in Ireland and Sweden) and MAXQDA (VERBI GmbH; in Belgium) for analysis. The researchers will also take brief notes during the interviews and focus groups to aid data interpretation and to identify potential themes. The interdisciplinary research team, with expertise spanning social, health, and sports psychology, human-computer interaction, and health care innovation, will actively engage in reflexive practice throughout the analysis. This collaborative approach will ensure participant voices are central while critically accounting for researchers’ potential biases shaped by their backgrounds.

Collaborative qualitative analysis will be used to thoroughly examine interview data, leveraging multiple researchers’ perspectives to capture nuances, manage large datasets, and reduce individual biases [53-55]. A hybrid thematic analysis approach will be used, combining inductive and deductive techniques based on Fereday and Muir-Cochrane’s framework [56]. The research questions, an initial literature review, and a preliminary examination of interview data shaped the deductive approach’s creation of a preliminary codebook. Simultaneously, the inductive approach will be used to identify new themes during coding, enriching the analysis. The transcripts will be coded using thematic categorizations, including within and between groups where applicable (eg, for trial arms 1 and 2 participants and for staff in different partner organizations).

The collaborative qualitative analysis framework will be applied with six sequential stages, commencing after the collection and transcription of the data: (1) preliminary organization and planning, (2) open and axial coding, (3) development of a preliminary codebook, (4) pilot testing the codebook, (5) final coding, and (6) reviewing the codebook and finalizing the themes. Consensus meetings will be conducted within and across trial sites to prepare the codebook and collaboratively identify and refine the themes. This approach ensures that diverse perspectives are considered, enhancing the validity and richness of the analysis throughout the research process.

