#### Person With Multimorbidity Participants

All participants will complete baseline questionnaires capturing their demographic, QoL, health, psychological and psychosocial, HCU, and multimorbidity self-management information (Table S1 in Multimedia Appendix 2) [39-48]. To reduce participant burden, questionnaires can be completed over 10 days. Data will be collected and managed using REDCap (Research Electronic Data Capture) software [49,50], hosted at Vrije Universiteit Brussel. Data collection mode will depend on participant preference. Those comfortable with technology will receive an email link; others will receive paper questionnaires, returned by post or collected during home visits for technology deployment (trial arms 1 or 2). Researchers may assist participants during these visits. For trial arm 3 participants, assistance will be provided via phone or online call, with researchers recording responses. When calls are not possible, a home visit will be arranged. Up to 60 participants in each of trial arms 1 and 2 (20 per country in Ireland, Belgium, and Sweden) will also take part in qualitative interviews to capture baseline information on current self-management strategies and trial expectations. Interview themes are detailed in Table S2 in Multimedia Appendix 2, while the T1 interview protocol is outlined in Multimedia Appendix 3. Interviews will be audio-recorded, transcribed, annotated, and analyzed.

All participants will complete QoL and HCU questionnaires at trial start (T1) and end (T2). As HCU is a key outcome, participants will report monthly to improve recall with data captured through REDCap either online or via researcher-assisted calls.

At trial completion, participants will again complete questionnaires (Table S1 in Multimedia Appendix 2), within a 10-day period, but if extenuating circumstances exist (eg, if participants are on holiday), within a 4-week period. Semistructured interviews with up to 60 participants in each of trial arms 1 and 2 will explore experiences using ProACT, self-management strategies, symptoms, and care network roles (themes in Table S2 in Multimedia Appendix 2, full interview protocol in Multimedia Appendix 4).

System use data (eg, technology engagement metrics and health data from sensors) and triage service use (eg, call frequency) will be continuously collected through the ProACT platform throughout the 6-month trial (Table S2 in Multimedia Appendix 2).

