### Sample Size Justification

We used a 3-group comparison (ie, trial arms 1, 2, and 3) as the main fixed effect for a repeated measures ANOVA model to determine the sample size of the p-RCT. For a desired power of 0.80, an error variance of 2, and a type I error rate of 0.05 with an attrition rate of 30%, we estimated that we need 76 participants per arm per trial site (rounded up to 80) to detect a standardized effect size (Cohen *d*) of 0.25. In the situation that recruitment targets have been met and more participant candidates can be included in the study, we will aim for a sample size of 100 per arm per trial site instead of 80 to obtain a power of 0.90. Sample size and power analysis were conducted using STATA (version 17.0; StataCorp LLC).

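### The primary QoL model neither adjusts for the T1 value nor states a common T1 mean, so fitted in the usual way it gives up precision that the collected baseline data could supply

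*Protocol article*

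**What the plan says.** The Data Analysis Plan section of the protocol article sets one linear mixed model for both primary outcomes. On its levels it says that "repeated measures of QoL or HCU will comprise the first level", with participants at the second level. The outcomes are then assessed "using fixed effects of time, treatment arm and time interaction, and other baseline covariates such as age and gender". The T1 value of the outcome does not appear among the named covariates, although the list is open-ended. The section does not say whether the T1 means may differ by arm.

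The timing is in the section on participants with multimorbidity: "All participants will complete QoL and HCU questionnaires at trial start (T1) and end (T2". For HCU it adds: "As HCU is a key outcome, participants will report monthly to improve recall". QoL therefore has two occasions and HCU has more.

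The Sample Size Justification takes the three-arm comparison "as the main fixed effect for a repeated measures ANOVA model to determine the sample size". It gives an error variance, a power, a type I error rate and 30% attrition, but no correlation between T1 and T2.

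**The concern.** T1 is collected before the intervention can act, and arms are randomised, so the true T1 means are equal. A model that estimates a separate T1 mean for each arm spends information on differences known to be zero. With two occasions, the usual factorial model (time, arm, arm-by-time) then returns the difference in mean change. An analysis that holds the T1 means equal, or regresses T2 on T1, targets the same effect with smaller variance.

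The plan's list of terms can be fitted in more than one way, and the choices give different standard errors. At stake is the width of the confidence intervals for a primary outcome. The T1 data are already collected from everyone, and the Results section reports the trial complete in Ireland and Belgium, so the analysis wording is one of the few remaining ways to gain precision.

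**Working it through.** **The plan's own figure.** A three-group F test with effect size f = 0.25 and alpha 0.05 needs 53 evaluable per arm for power 0.80. Then 53/(1 − 0.30) = 75.7, rounded up to the stated 76 per arm per site. For power 0.90 it needs 69, and 69/0.70 = 98.6, rounded up to 99 (stated 100). This works only if 0.25 is read as Cohen f; the section labels it Cohen d. That is a separate matter and nothing below depends on it. What matters here is that no T1–T2 correlation is stated, so r has to be assumed.

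**Inputs.** QoL at T1 and T2; 80 per arm per site; 30% attrition (all from the protocol article). Assumed: outcome SD 1 at both times, r from 0.5 to 0.8.

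**Complete data, n per arm, contrast between two arms:**

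- Time, arm and arm-by-time: variance 2 × 2(1 − r)/n, the difference in mean change. Simulated mixed-model fits agreed with the difference in mean change to within rounding error.
- Common T1 mean, or ANCOVA of T2 on T1: variance 2(1 − r²)/n.
- Ratio of the second to the first: (1 − r²)/[2(1 − r)] = (1 + r)/2.

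**What the listed terms can mean, at r = 0.6 and n = 80:**

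- Usual factorial, arm-by-time term: √(2 × 0.80/80) = 0.1414.
- Time plus arm-by-time, coded so that the arms share one T1 mean (four mean parameters for three arms and two times): √(2 × 0.64/80) = 0.1265, the same as ANCOVA.
- Time plus arm-by-time with time as a factor and no such coding: the terms expand to all six arm-by-time means, so the model is saturated again. The arm coefficient at T2 is the unadjusted T2 difference: √(2/80) = 0.1581.

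Leaving out the arm main effect is therefore not enough. The common T1 mean must be coded explicitly.

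**With attrition.** Let a fraction p = 0.70 have T2, let all have T1, and let dropout be unrelated to outcome. Per arm, the factorial model has variance (1 − r²)/(pn) + (1 − r)²/n, and the common-T1 model has (1 − r²)/(pn). The ratio is (1 + r)/[(1 + r) + p(1 − r)]. At r = 0.6 this is 1.6/(1.6 + 0.28) = 0.851, with standard errors of 0.1639 and 0.1512 for n = 80.

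| Assumed r | Ratio, complete | Saving | Ratio, 30% attrition | Saving |
|---|---|---|---|---|
| 0.5 | 0.75 | 25% | 0.811 | 19% |
| 0.6 | 0.80 | 20% | 0.851 | 15% |
| 0.7 | 0.85 | 15% | 0.890 | 11% |
| 0.8 | 0.90 | 10% | 0.928 | 7% |

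With attrition, the saving is worth 1/0.811 = 1.23, 1/0.851 = 1.18 and 1/0.890 = 1.12 times the participants at r = 0.5, 0.6 and 0.7.

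**HCU.** Monthly reports give more than two occasions, so these two-point figures do not apply, and no figure is offered for HCU.

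**The case against.** The strongest reply is that the sentence, read by its punctuation, names time, the arm-by-time interaction and covariates, and no separate arm main effect. With suitable coding that is exactly the common-T1 model, and it loses nothing. This stands as a possible reading. A reader might infer from T1 being an outcome row that the plan must be a change-score analysis with wider intervals; the text does not support that as a fact. It also does not secure the efficient model, because the same list with time as a factor reproduces the saturated model.

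A second reply is that the arm main effect is imported from the Sample Size Justification, which sizes the trial and does not define the analysis. That is fair. A reader might go further and infer that the arm main effect is itself the tested term, so that a T2 effect is averaged with a zero T1 effect and halved. The Data Analysis Plan never says that the marginal arm effect is tested, so that inference is not supported.

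Third, a difference in mean change is valid and unbiased in a randomised trial, the covariate list is open, and a condensed article may leave such detail to a fuller plan. All of this is true, and it limits the point to efficiency. But the article does set out the primary model, and the model as worded leaves an available gain unsecured.

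Fourth, the complete-data savings overstate the case under the protocol's own 30% attrition, and they do not describe HCU. Both corrections are accepted in the figures above.

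**Conclusion.** The point holds as one about efficiency. As worded, the primary model neither adjusts QoL for T1 nor fixes a common T1 mean. Fitted in the usual way, it has 2/(1 + r) times the variance of a baseline-adjusted estimate with complete data. Adjustment saves 25% to 10% of that variance over an assumed r of 0.5 to 0.8. With 30% of T2 missing, the saving is about 19%, 15% and 11% at r = 0.5, 0.6 and 0.7. Under the coding with no arm difference at T1, the loss is nil.

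These sizes rest on an assumed r, equal T1 and T2 variances, and dropout unrelated to outcome. The change-score description is exact only for QoL with complete data. There is no claim of bias, of a halved effect, or of a quantified loss for HCU. The change is worth making because the common-T1 model is never less precise than the usual fit under these assumptions.

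**What to change.** For QoL, state that the mixed model has one T1 mean common to all arms, with arm-by-time terms at follow-up only; an ANCOVA of T2 on T1 is an equivalent choice. Name the T2 arm contrast as the primary effect. Both parts are needed: naming the T2 contrast without the common T1 mean could yield the unadjusted T2 difference.

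For HCU, enter the T1 value as a covariate rather than as a row sharing a mean with the monthly reports. The T1 recall window is not given in the article and may differ from one month, in which case the two are not on the same scale.

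The cost is a sentence or two of analysis wording, best fixed before the outcome data are compared by arm. It needs no new data and no change to the design.

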The primary outcomes for participants with multimorbidity include QoL and HCU.

The secondary outcomes include self-management (ie, assessed via a mixed methods approach; eg, this includes an examination of participants’ perceived self-management using the custom-designed questionnaire and interviews with participants to explore their use of ProACT), health status (eg, an exploratory examination of the impact of ProACT on the hypothesized stabilization or reduction of participants’ symptoms using the system data), quality of health care support, and other issues of relevance include multimorbidity self-management knowledge, attitudes (eg, confidence in ability to self-manage), and skill; health literacy, digital literacy, and associated attitudes (eg, attitudes toward technology).

Other outcomes for participants with multimorbidity include: the usability, accessibility, and acceptability of, and engagement, satisfaction, and overall experiences with, ProACT.

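### Health care use by arm is given two non-equivalent analyses with neither named as primary, and the Poisson option as named would understate uncertainty if the counts are overdispersed

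*Protocol article*

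**What the plan says.** Under Person With Multimorbidity Participants the protocol states: "The primary outcomes for participants with multimorbidity include QoL and HCU". On data collection the same section says that "participants will report monthly to improve recall with data captured through REDCap".

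The Data Analysis Plan then describes two analyses of HCU.

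- **First analysis.** For differences in "HCU between the arms, a linear mixed model will be used". Its structure is explicit: "repeated measures of QoL or HCU will comprise the first level, and participants will comprise the second level in the hierarchy". Fixed effects are time, the arm-by-time interaction and baseline covariates.
- **Second analysis.** The economic evaluation is introduced next: "For the monetary value, the HCU data will form the basis of the analysis". The following paragraph says that, because the questionnaire mixes count and yes/no items, "the analysis will make use of 3 statistical models: Poisson (countable data), logistic (binary response data), and linear regression (continuous data". The purpose is given as: "The analysis will allow the observation of how ProACT affects the HCU, per arm at each trial site, and what the costs involved" in that effect are.

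The paragraph closes by offering the bootstrap, as an example only, for the confidence interval of the cost-effectiveness estimate. The section opens by listing QoL, HCU and cost-effectiveness together as the three analyses for the primary outcomes.

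**The concern.** One question, whether ProACT changes HCU, is given two answers that need not agree. The protocol also justifies the second set by the type of the HCU items. That reason applies equally to the HCU data that the linear mixed model is to analyse, so the text does not explain why one outcome is treated in two ways.

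The second worry is precision. Some people use far more care than others, and the same person contributes a report every month. A Poisson model with no participant effect and no dispersion term treats the variance of the counts as equal to their mean. If it is larger, standard errors are too small, and chance differences between arms are declared significant too often.

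Timing adds weight. The trial is unblinded, is complete in Ireland and Belgium, and was due to finish in Sweden by March 2026. A choice of primary model left open while data are in hand is open to the charge that it was made after seeing results.

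**Working it through.** **1. The two analyses side by side**

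| | First analysis | Second analysis |
|---|---|---|
| Model | Linear mixed | Poisson, logistic or linear, by item type |
| Effect scale | Mean difference | Rate ratio, odds ratio or mean difference |
| Pooling | Arms compared, no split by site stated | Per arm at each site |
| Participant level | Stated | Not stated |
| Stated role | Test for differences between arms | Effect on HCU, then its cost |
| Named as primary HCU result | No | No |

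They are not equivalent. Nor is HCU defined as one count, a set of items or a cost.

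**2. What Poisson does under overdispersion**

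The protocol states no HCU mean, variance or dispersion, so it has no figure of its own to reproduce here. Let φ be the variance-to-mean ratio of a participant's count over follow-up. The range of φ is an assumption.

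- Poisson interval width as a share of the correct width: 1/√φ
- True type I error of a nominal 5% test: 2 × (1 − Φ(1.96/√φ))
- True coverage of a nominal 95% interval: 1 minus that error

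Example at φ = 2: 1/√2 = 0.71, 1.96/√2 = 1.386, and 2 × (1 − Φ(1.386)) = 0.17.

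| φ (assumed) | Width share | Type I error | Coverage |
|---|---|---|---|
| 1 | 100% | 0.05 | 95% |
| 1.5 | 82% | 0.11 | 89% |
| 2 | 71% | 0.17 | 83% |
| 3 | 58% | 0.26 | 74% |
| 4 | 50% | 0.33 | 67% |
| 6 | 41% | 0.42 | 58% |

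**3. Check by simulation**

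Arm sizes follow from the protocol's 30% attrition: 80 × 0.7 = 56 per arm at a site, and 240 × 0.7 = 168 per arm overall. Negative binomial counts with no arm effect were simulated, with means of 2 and 6 and 4000 runs per setting. The Poisson test rejected in 16% to 17% of runs at φ = 2, about 32% at φ = 4, and 41% to 43% at φ = 6. Over the whole range of φ, a robust variance gave 4.6% to 6.2%, and a participant-level comparison of means gave 4.5% to 6.0%.

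**4. Why monthly reporting matters**

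Suppose the monthly mean is m and people differ by a multiplicative factor with variance v that stays constant over six months. Then φ is 1 + mv for one month and 1 + 6mv for the six-month total.

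- m = 0.5, v = 0.5: φ is 1.25 monthly and 2.5 over six months.
- m = 1, v = 1: φ is 2 monthly and 7 over six months.

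Poisson on the pooled monthly rows, comparing arms on overall use, had type I error of 0.23 and 0.44 in these two cases. A participant-level comparison gave about 0.05 in both. Overdispersion that looks mild in any one month therefore becomes large once the months are pooled without a participant effect.

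**5. The linear mixed model under the same kind of data**

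With a balanced random-intercept model, six monthly gamma-Poisson counts per person, 56 or 168 per arm, monthly means of 0.1 to 1.67 and v of 0.5 to 2, type I error was 0.044 to 0.056 for arm and 0.043 to 0.053 for arm by linear time.

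**The case against.** The strongest reply is that the text contains no conflict. Only the linear mixed model is tied to a test of significance between arms. The Poisson, logistic and linear set comes after the economic evaluation has been introduced, feeds the monetary value, and is followed by an interval for the cost-effectiveness estimate. On that reading the mixed model is primary and the rest is costing. This largely stands: a reader might infer two flatly contradictory primary analyses, but the text supports only an unresolved overlap. The overlap does not disappear, because the stated purpose of the second set is the effect on HCU first and its cost second, and cost-effectiveness is itself listed among the analyses for the primary outcomes.

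A second reply is that naming Poisson in a condensed article does not exclude random effects, robust errors or an exposure term, which an analysis plan may specify. That is fair. The missing detail alone would not be a finding. It matters because the same section does name a participant level for one HCU model and not for the other. The bootstrap does not close the gap either, since it is offered only for the cost-effectiveness estimate.

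A third reply is that the size of the Poisson problem rests on assumed dispersion. That is correct, and at φ = 1 there is no harm.

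**Conclusion.** The point holds as an unresolved overlap with a conditional consequence. The protocol gives two non-equivalent analyses of HCU by arm and does not designate the primary one. If the Poisson model as named supplies HCU intervals, they are too narrow whenever people differ in their underlying rate of use. That is likely for repeated counts per person, but the documents do not quantify it. Over an assumed φ of 1 to 6, type I error runs from 5% to about 42%; modest values of 1.5 and 2 give about 11% and 17%.

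Two stronger readings are not supported. The intervals cannot be called far too narrow as a fact, because no dispersion is given and the upper figures belong to the upper assumptions. Nor does it follow that neither model suits the data. Skewed counts with zeros may cost the linear mixed model efficiency, but it held close to 5% in the settings examined, and a mean difference is a legitimate target and useful for costing.

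**What to change.** - Designate one primary HCU variable and one primary model for it, and state that choice before the HCU analysis.
- Label the other set as belonging to the economic evaluation or as supportive. Keeping the linear mixed model as primary would be acceptable.
- Wherever count items are modelled with Poisson, use participant-clustered robust variance, or replace it with a negative binomial mixed model with a participant random intercept. Add an offset for the time each report covers, since people who leave early contribute less time.
- For binary items, use the matching mixed or participant-clustered logistic model.

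The cost is a few sentences of analysis wording, with no change to data collection or sample size. HCU intervals will be somewhat wider than plain Poisson would show; under overdispersion that is their correct width.
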